#### Methods for additional analyses

2.6.1

Mediation modelling will be performed to investigate the hypothesis that improvements in times to relapse under Open Dialogue are brought about by enhanced quality/size of the social network or by higher levels of shared decision-making. Specifically, we will estimate the direct (non-mediated by networking) and indirect (mediated by networking) effects of Open Dialogue on time to relapse. For this purpose, social network quality, social network size, and shared decision-making at 6 months will be assessed as potential mediators. Confounders of the relationship between network quality and relapse (e.g. social network score or symptom severity at first research interview) will be measured and included in the mediation modelling. A complier average causal effect (CACE) analysis will also be undertaken to estimate the effect of actually receiving the intervention using instrumental variables regression.

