### Outcomes

2.5

The primary outcome is time, in days, to ‘relapse’ following recovery. Recovery is defined as the absence of significant symptoms and presence of adequate social functioning; and relapse as the return of significant symptoms and deterioration of social functioning [7]. A summary of each participant's social circumstances, mental health, and type of response from health care providers for the two-year follow-up period is created primarily from their electronic medical records and research contacts. This summary is reviewed by a panel of trained raters, blind to treatment allocation, who use it to estimate the presence and date of any recovery or relapse using an established method [7]. Any information that might unblind the panel is redacted, and the panel's estimation of allocation is monitored.

For a description of secondary outcomes, measures, potential mediators, and family/carer measures see Table 1 below.

**Table 1 t0005:** Details of secondary outcomes, potential mediators, and family/carer measures.

	Outcome	Measure	Description of measure
Secondary outcomes	Recovery	Time in days to initial recovery, and the total number of days spent in recovery [7]	An expert panel estimate based on 24 monthly summaries of a person's social circumstances, mental health, and type of response from healthcare practitioners. See assessment method described for the primary outcome measure.
	Service-user defined recovery	Questionnaire on the Process of Recovery (QPR) [40]	A 15-item self-report measure developed to assess intrapersonal and interpersonal functioning, measured at 3, 6, 12, and 24 month time points (test-retest reliability *r* = 0.769 [40]).
	Health-related quality of life	EQ-5D-5L [25]	A self-report measure yielding a 5-digit number describing self-rated health state measured, during the first research interview, and at 3, 6, 12, and 24 months post initial crisis presentation **(**intraclass correlation coefficient = 0.75 [30]).
	Service use and societal costs	Client Service Receipt Inventory (CSRI) [8] Plus the number of and length in days of psychiatric admissions, and number of accepted referrals to crisis services in the 24 months after the initial crisis	A tool used to collect information on service utilisation, accommodation, income, and other costs measured at 3, 12, and 24 months post the initial crisis presentation.

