	Service user satisfaction	Client Satisfaction Questionnaire (CSQ-8) [6]	A self-report measure of service user overall satisfaction with care measured at 3, 6, and 24 months post initial crisis presentation (alpha coefficient, 0.83 to 0.94 [2]).
Potential mediators	Social network quality and size	Social Provisions Scale (SPS) [15]	A 24-item self-report measure that examines the degree to which respondent’s social relationships provide the dimensions of social support using a model of social provisions [60] measured during the first research interview, and at 3, 6, 12, and 24 months post initial crisis presentation. Scores range between 24 and 96 with a higher score indicating a greater degree of perceived support indicative of higher quality social networks (alpha coefficient, 0.89 [12]).
		Lubben Social Network Scale (LSNS-6) [33]	A 6-item self-report scale that assesses the size, closeness, and frequency of contacts of a service user's social network (family and friends), providing a total score between 0 and 30 during the first research interview, and at 3, 6, 12, and 24 months post initial crisis presentation. (alpha coefficient, 0.78 [12]).
	Shared decision making	The Modified Dyadic OPTION scale [36]	Assesses the degree to which clinicians involve patients in shared decision making through observer rating of clinician behaviour, measured at 3, 6, and 24 months post initial crisis presentation (alpha coefficient 0.9 [41]).
Family/carer outcomes	Carer satisfaction	Client Satisfaction Questionnaire (CSQ-8) [6]	A self-report measure of carer overall satisfaction with care measured at 3, 6, and 24 months.
	Carer burden	The Burden Assessment Scale [49]	A 19-item self-report measure completed by the primary caregiver to assess perceived objective and subjective consequences of providing care to a service user, measured at 3, 6, and 24 months, (alpha coefficient, 0.92 [27]).
	Shared decision making	The Modified Dyadic OPTION scale [36]	Assesses the degree to which clinicians involve carers in shared decision making through observer rating of clinician behaviour, measured at 3, 6, and 24 months.

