### Statistical analysis

2.6

The primary outcome, time to relapse from recovery, will be analysed using Cox regression, where time to relapse will be the dependent variable, with fixed explanatory variables of trial arm, and stratification factor (catchment area of the mental health service), and cluster-level balancing variables of general practice list size, and Index of Multiple Deprivation. The model will also contain a random intercept that varies at the level of the catchment area to account for general practice cluster effects.

This modelling will supply an estimate of the hazard ratio of relapse comparing Open Dialogue with TAU and an associated 95% confidence interval. In the (unlikely) event that covariates are missing or that aspects of the Open Dialogue intervention (e.g. number of contacts between participants and teams) drive censoring times, we will employ multiple imputation for survival outcomes as described in White and Royston [61].

Continuous secondary outcomes measured at several time points will be analysed using linear mixed models. In these models the available post-allocation measures of the secondary outcome variables form the dependent variable, with trial arm, time, trial arm x time interactions terms, stratification, and balancing variables as explanatory variables. To account for the correlation between repeated measures taken on the same subject, subject-varying random effects will be included in the model. To account for remaining correlation between outcomes from patients from the same cluster, a further cluster-varying random intercept will be included in the model.

Distributional assumption will be checked and continuous outcomes arising from skewed distributions suitably transformed before analysis.

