#### Baseline and follow-up research interviews

4.2.1

The baseline timepoint is the date of the crisis referral. This referral takes place after cluster randomisation, but before a potential participant has been assessed as meeting eligibility criteria prior to consent. The first research interview is conducted as close as possible to the date of the crisis referral (baseline) after consent is provided. Research interviews either occur in person (i.e. at the research site or at participant's homes) or over the telephone (the primary method of data collection during the COVID-19 pandemic). Follow-up interviews are undertaken at 3, 6, 12, and 24 months from baseline (see Fig. 1).

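### Mediators measured at 6 months are related to all relapses after recovery, so for participants who relapse before month 6 the mediator is measured after the outcome

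*Protocol article*

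**What the plan says.** All references are to the protocol article.

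- **Mediators and their time point** (Methods for additional analyses): "social network quality, social network size, and shared decision-making at 6 months will be assessed as potential mediators".
- **Outcome of the mediation model** (same section): direct and indirect "effects of Open Dialogue on time to relapse". No restriction on when the relapse occurs is given.
- **Clock for the interviews** (Baseline and follow-up research interviews): "The baseline timepoint is the date of the crisis referral", and "Follow-up interviews are undertaken at 3, 6, 12, and 24 months from baseline".
- **Clock for the outcome** (Statistical analysis): "The primary outcome, time to relapse from recovery, will be analysed using Cox regression". Under Outcomes, a blinded panel dates recovery and relapse from a summary of the whole two-year follow-up, so months 0 to 6 are included.
- **Definition** (Outcomes): "relapse as the return of significant symptoms and deterioration of social functioning".
- **Confounders** (Methods for additional analyses), given as examples: "social network score or symptom severity at first research interview".
- **Earlier mediator values** (Tables 1 and 2): both network scales are collected at the first research interview and at 3 months. Shared decision-making is first collected at 3 months; Table 1 describes its scale as a rating of how far "clinicians involve patients in shared decision making through observer rating of clinician behaviour, measured at 3, 6, and 24 months post initial crisis presentation".

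**The concern.** A mediator has to precede the outcome whose effect it carries. Here the two run on different clocks: the mediator is fixed at six months from referral, while the outcome starts at recovery, which may come well before that. For anyone who recovers and relapses inside six months, the score may be a consequence of the relapse.

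This is plausible because relapse is itself partly defined by worse social functioning, and two of the three mediator constructs are measured with social-network scales. Covariates from the first interview cannot remove the effect of a relapse that happens between that interview and month 6.

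What is at stake is the explanatory claim. Mediation is listed among the objectives and taken up again in the Discussion. A network score lowered by early relapse would look protective even if it had no influence on relapse, and part of the treatment effect could be wrongly attributed to it.

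**Working it through.** **1. The plan's own figures (Sample size section).** Freedman's formula with HR 0.589, two-sided 5% (sidedness assumed) and 90% power: (1.960 + 1.282)² × (1.589/0.411)² = 157.06, stated as 157. Design effect 1 + 17 × 0.04 = 1.68, and 157 × 1.68 = 263.8, stated as 264. Then 264/0.49 = 538.8, stated as 538. The figures reproduce to rounding, and the present point does not touch them. The article gives no figure for the mediation analysis.

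**2. Can a relapse precede the mediator?** Yes. Recovery at month 2 and relapse at month 4 is an ordinary path under the definitions; the mediator is then measured two months after the event. For a participant who recovers after month 6, the mediator comes before the period at risk and the order is correct.

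**3. How many relapses might be affected?** No recovery timing is given, so it is assumed: exponential time to recovery with rate a = ln 2/median, then a constant relapse hazard b after recovery. The probability of having relapsed by month t is

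F(t) = 1 − [b·exp(−a·t) − a·exp(−b·t)]/(b − a),

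with b chosen so that F(24) = 0.49, the plan's average relapse rate.

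| Median recovery (months) | a | b | F(6) | F(6)/0.49 | Of 264 |
|---|---|---|---|---|---|
| 1 | 0.693 | 0.030 | 0.127 | 26% | 69 |
| 2 | 0.347 | 0.032 | 0.104 | 21% | 56 |
| 3 | 0.231 | 0.035 | 0.089 | 18% | 48 |
| 4 | 0.173 | 0.038 | 0.080 | 16% | 43 |
| 6 | 0.116 | 0.046 | 0.070 | 14% | 38 |

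**4. How large is the bias?** Simulation with 400,000 participants per scenario. The mediator is standard normal and has no effect on relapse. A relapse before month 6 lowers the 6-month score by an assumed 0, 0.3 or 0.5 SD. A Cox model of time from recovery to relapse on the 6-month score is fitted first to everyone who recovers. It is then refitted with a 6-month landmark (relapse-free at 6 months, clock from the later of 6 months and recovery). The true HR is 1.00.

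| Assumed fall | HR per SD, all relapses | Approx. false-positive rate at 264 events | HR per SD, landmark |
|---|---|---|---|
| 0 SD | 1.00 | 5% | 1.00 |
| 0.3 SD | 0.93-0.96 | 10-22% | 0.995-1.003 |
| 0.5 SD | 0.89-0.94 | 17-51% | 0.995-1.005 |

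Ranges run over the recovery medians in step 3; earlier recovery gives the larger bias. The simulation leaves out clustering, an arm effect and missing mediator values.

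**5. What each remedy keeps.** The 6-month landmark keeps about 195-227 of 264 relapses. For a cut at month 3 the same F gives F(3) = 0.050 at median 1 and 0.020 at median 6. That is 264 × 0.050/0.49 ≈ 27 and 264 × 0.020/0.49 ≈ 11 relapses set aside, leaving about 237-253.

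**The case against.** **Detail left to the SAP.** The article defers details of additional analyses to an SAP that is not shown, and a landmark or risk-set rule is the kind of thing an SAP adds. It is right that the SAP may already deal with this. But the article does more than stay silent: it fixes the mediator at one time point and sets it against an outcome that can occur earlier. Followed as written, it produces the wrong order for some participants.

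**Bias is not automatic.** Correct. If relapse leaves the score unchanged, the HR stays at 1.00. The size of the fall is assumed. For shared decision-making, rated from clinician behaviour, even its direction after relapse is unknown.

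**The remedy has its own price.** Also correct. A landmark conditions on being relapse-free, which treatment may affect, and changes the effect being decomposed. Month 3 allows less time for the mechanism to act.

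Stronger readings that the documents do not support:

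- A reader might start the risk of relapse at the crisis and conclude that about a third of relapses fall before month 6. Relapse can only follow recovery, so that is not a possible scenario.
- A reader might treat arm-specific relapse rates of 58% and 40% as planned. They can be back-calculated from HR 0.589 and the 49% average, but the article does not state them.
- A reader might infer that first-interview confounders should give way to data from the six months before the crisis. That interview does follow the referral, but it is to be held as soon after it as possible. According to Table 2, the earlier records hold no network scale and no BPRS. Replacing the interview scores would drop the very confounders that the article names.

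**Conclusion.** The point holds: as written, the mediation analysis lets some relapses precede their mediator, and the named covariates cannot correct for it. Under the assumed recovery medians of 1 to 6 months, constant hazard after recovery and 49% relapse, this concerns about 14-26% of relapses (38-69 of 264). If an early relapse lowers the score by 0.3-0.5 SD, a mediator with no effect shows an HR of about 0.89-0.96 per SD. The ordering problem follows from the text; its size rests on these assumptions, since the documents give neither recovery times nor the effect of relapse on the scores.

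It would go too far to infer that a spurious association is certain, or that the trial's main result is in doubt. Participants who recover after month 6 are unaffected, and so is the primary comparison. The issue is confined to a secondary, explanatory analysis, but one that answers a stated objective.

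**What to change.** State in the SAP, before database lock, that the mediator must precede every relapse analysed. Two options use data already collected:

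1. Take the 3-month mediator values and analyse only relapses after month 3.
2. Keep the 6-month values with a 6-month landmark: include participants relapse-free at 6 months and start the clock at the later of 6 months and recovery.

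Keep the first-interview network and symptom scores as confounders in either case. Pre-crisis record data may be added but cannot replace them.

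The cost is wording plus three limits to report with the result. Relapses before the cut are not used (about 11-27 of 264 under option 1 and 37-69 under option 2, on the assumptions above). The analysis conditions on being relapse-free at that point, which treatment may affect. The direct and indirect effects then describe later relapse only, not the whole effect on time from recovery to relapse. If the SAP already contains such a rule, confirming it is enough.

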### Objectives

2.1

Primary objective: To examine whether Open Dialogue is more effective than TAU at increasing time to relapse after recovery.

Secondary objectives: To examine whether Open Dialogue is more effective than TAU at:-Reducing time to initial recovery, increasing overall days spent in recovery, and increasing service-user defined recovery-Reducing service use and societal costs and improving health-related quality of life-Increasing service-users' satisfaction with care

We will examine whether social network quality, social network size or shared decision-making mediate the impact on the primary outcome. Additionally, we will examine the experience of carer burden, shared decision-making, and satisfaction with care for the family/carers of a subsample of trial participants offered Open Dialogue or TAU.

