## Intervention delivery

3

Open Dialogue teams offer care from initial presentation in crisis through to discharge from the service, typically through ‘network meetings’ which include the service user, people they identify as important to them such as family members, and two or more Open Dialogue Practitioners. The agenda is set by the network, and there is a strong emphasis on service-user participation in any treatment decisions. Wherever possible, the same practitioners remain with the network throughout. Teams are multidisciplinary, typically including nurses, social workers, peer practitioners, clinical psychologists, occupational therapists, and psychiatrists, all of whom have undertaken an Open Dialogue training programme. Services are underpinned by the seven key principles of Open Dialogue: (1) Immediate Help; (2) A Social Network Perspective; (3) Flexibility and Mobility; (4) Responsibility; (5) Psychological Continuity; (6) Tolerance of Uncertainty; and (7) Dialogue and Polyphony [56]. They are ‘needs-adapted’ and network meetings take place as little or often as required by the network, perhaps occurring twice weekly in the time immediately after referral, moving to weekly or fortnightly as treatment progresses, whilst also working flexibly in collaboration with other services [48]. There is an ‘open discharge policy’, with service users able to ask for further network meetings at any point after discharge from the service, ideally with the same practitioners.

TAU is current routine crisis care and continuing community care, as delivered by English mental health services. This is based on a model which comprises a number of multi-disciplinary teams, the provision of care coordination, and a range of community and in-patient interventions and support.

 Participants in both trial arms may be offered any intervention they would ordinarily have access to individual psychological and pharmacological interventions, social, and housing support. The duration of contact is determined by each team, based on clinical need. Those with complex problems may receive continuing care for the duration of the study. Open Dialogue is not offered to those in the TAU arm. The provision of mental health services after the follow-up period has ended will be the responsibility of the participants' current mental healthcare provider.

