### Participant recruitment and retention

4.1

If a person presents to services and appears eligible, a local staff member asks if a researcher can make contact. Those who agree are contacted by a researcher with further information, and after time to consider (usually 48 h or as long as they need), they are asked for informed consent. If they lack capacity, consent via a personal (relative or friend) or nominated consultee (a local senior clinical professional consultee with no other involvement with the trial) may be sought [58], and reviewed at the point they regain capacity. Separate informed consent is sought from the family and carers of a purposive sub-sample of trial participants for questionnaires, and from all who attend a network meeting to audio-record that meeting.

Participants are also given a £15 shopping voucher for each interview and are reimbursed for any additional expenses (e.g. travel). For those participants who choose to withdraw from further participation, agreement is sought for access to their electronic medical records for the remainder of the study to allow for the primary clinical outcome to be collected.

Research staff are located within NHS sites, closely engage with clinical teams, and receive regular training, support, and supervision to effectively engage participants. Regular meetings with site-based Principal Investigators (PIs) and other senior clinical and management staff, and input from the Lived Experience Advisory Panel (LEAP) address any issues with participant recruitment and retention.

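### Network and symptom scores from the first research interview, named as confounders in the mediation model, may already be affected by treatment, so adjusting for them as ordinary baseline covariates could remove part of the network-mediated effect

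*Protocol article*

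**What the plan says.** The secondary aim in section 2.1 is: "We will examine whether social network quality, social network size or shared decision-making mediate the impact on the primary outcome". Section 2.6.1 fixes the time point: "social network quality, social network size, and shared decision-making at 6 months will be assessed as potential mediators". The same section lists examples of confounders of the relation between network quality and relapse, and commits to using them: "e.g. social network score or symptom severity at first research interview) will be measured and included in the mediation modelling".

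Other sections set the order of events.

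- **Time zero.** Section 4.2.1: "The baseline timepoint is the date of the crisis referral". On allocation it adds: "This referral takes place after cluster randomisation".
- **Interview.** Section 4.2.1: "The first research interview is conducted as close as possible to the date of the crisis referral (baseline) after consent is provided". No longest interval is stated. Section 4.1 puts a staff approach and researcher contact before consent, which is sought "after time to consider (usually 48 h or as long as they need"; a consultee may be involved where capacity is lacking.
- **Treatment.** Section 3 has Open Dialogue teams giving care from first presentation in crisis, lists immediate help as the first principle, and describes network meetings as "perhaps occurring twice weekly in the time immediately after referral".
- **Measures.** Table 2 has separate columns for the true baseline (the crisis) and the first research interview. SPS, LSNS-6 and BPRS first appear in the interview column. Only records data, covering the preceding six months, belong to the true baseline.

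**The concern.** An ordinary split into direct and indirect effects needs mediator–outcome confounders that the exposure has not affected. The scores named in section 2.6.1 are taken after allocation, after referral and possibly after the first network meetings. They also measure what the intervention works on: the person's network and symptoms.

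If the arms already differ on a score at the interview, conditioning on it blocks the route from Open Dialogue through the early score to the six-month network score and on to relapse. That route belongs to the effect that section 2.1 sets out to examine. The trial could then understate how far social networks carry any benefit, or report a decomposition that does not add up. How far this happens depends on how much has changed by the interview.

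**Working it through.** **The plan's own figures.** The article states no effect size or power for the mediation analysis, so there is no figure to reproduce. Its sample-size chain (157 × 1.68 = 263.8, given as 264 relapses; 264/0.49 = 538.8, given as 538 participants) does not use the interview scores and is not affected.

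**Order of events.** From sections 3, 4.1 and 4.2.1: cluster allocation → crisis referral (time zero) → Open Dialogue care available at once → approach, information, usually two days or more to consider, consent → first interview (SPS, LSNS-6, BPRS) → six-month mediators. The interview scores therefore come after the exposure is fixed. Whether they come after any treatment contact varies by participant, and the article does not report it.

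**Formula.** Take a linear path model in SD units. Let d1 be the arm effect on the interview score, d6 the arm effect on the six-month mediator, and r the slope of the six-month mediator on the interview score. Conditional on the interview score, the arm coefficient for the mediator is d6 − r × d1. With f = d1/d6, the share of the arm-to-mediator path lost is r × d1/d6 = r × f. The product indirect effect loses the same share.

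**Numbers.** The article gives none of d1, d6 or r. All values below are assumptions.

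| d6 | r | d1 = 0 | d1 = 0.02 | d1 = 0.05 | d1 = 0.10 |
|---|---|---|---|---|---|
| 0.5 | 0.4 | 0% | 2% | 4% | 8% |
| 0.3 | 0.6 | 0% | 4% | 10% | 20% |
| 0.2 | 0.8 | 0% | 8% | 20% | 40% |

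**Does the decomposition still add up?** Take d6 = 0.3, r = 0.6, d1 = 0.10, with outcome coefficients −0.4 (mediator), −0.2 (interview score) and −0.1 (arm).

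- True total: −0.1 − 0.2 × 0.10 − 0.4 × 0.3 = −0.240.
- True network-mediated effect: −0.4 × 0.3 = −0.120.
- Interview score in both models: indirect = −0.4 × (0.3 − 0.6 × 0.10) = −0.096, direct = −0.1, sum = −0.196.
- Missing: 0.044, made up of 0.024 lost from the indirect path and 0.020 from the route early score → outcome.

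A simulation of 1,000,000 subjects agrees: indirect −0.097 and sum −0.197 at d1 = 0.10, and indirect −0.107 at d1 = 0.05.

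**Should the scores simply be dropped?** No. In the same simulation, keeping the interview score in the outcome model but not conditioning the arm–mediator effect on it gave −0.119 (d1 = 0.05) and −0.121 (d1 = 0.10), close to −0.120. Replacing it altogether with a score from before treatment gave −0.129 and −0.130, about 7% to 8% too large, because the interview score still confounds mediator and outcome.

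This check is linear. It shows direction and mechanism, not the size on the hazard scale of a Cox model.

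**The case against.** Four objections carry weight.

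1. **No estimator is named.** Section 2.6.1 says only that the confounders will enter the mediation modelling, and gives the scores as examples. A method for exposure-affected confounders would fit that wording too, and sections 2.6.2 and 4.3 leave detail to the SAP. So the article does not commit to plain covariate adjustment. It does, however, choose these scores, call them confounders and say nothing of their timing. The point rests on that stated choice, not on missing detail.
2. **The interview may be early enough.** It is meant to follow referral closely, and the twice-weekly meetings are only a possibility. The introduction places gains in relationships in the longer term. Early divergence on perceived support or network size is therefore not evident from the article, and if there is none, nothing is lost. This stands and makes the point conditional.
3. **The scores are real confounders.** This also stands, and it rules out deleting them.
4. **The scope is narrow.** Shared decision-making is first measured at 3 months, so it cannot be adjusted for its own interview value.

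A reader might go further and infer three things that the article does not support. The first is that the analysis will certainly understate mediation; this needs an arm effect by the interview, which is unknown. The second is that the early gain is reclassified as direct effect; with the score in both models it leaves both paths, as the sum of −0.196 against −0.240 shows. The third is that a particular loss is established. For example, r = 0.7 with f = 0.2 or 0.5 gives 14% or 35%, but both inputs are assumed, and f = 0.5 would need half the six-month effect to be present at an interview held soon after referral.

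**Conclusion.** The point holds in conditional form. The scores named as confounders are measured after allocation and possibly after treatment has begun, so they cannot be taken as pre-exposure covariates. If they are adjusted for as such, the network-mediated effect loses the share r × f and the two effects no longer sum to the total. The loss is nil with no early effect, 10% to 20% at d6 = 0.3, r = 0.6 and d1 = 0.05 to 0.10, and about 2% to 40% over the wider ranges tried (d6 0.2 to 0.5, r 0.4 to 0.8, d1 0.02 to 0.10). None of these inputs comes from the article.

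Only the secondary mediation analysis is concerned, chiefly its network mediators. The primary Cox model in section 2.6 does not include the interview scores. The matter should be settled before analysis, but it does not threaten the trial's main result.

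**What to change.** State in the SAP, before database lock:

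- **Pre-exposure confounders.** Use the records data for the six months before referral (diagnoses, admissions, crisis referrals, service contacts) and fixed sociodemographics.
- **Interview scores.** Keep first-interview SPS, LSNS-6 and BPRS, but treat them as possibly exposure-affected intermediate confounders, using interventional direct and indirect effects or sequential g-estimation.
- **Comparison.** Report these results beside the plainly adjusted estimate, so that readers can see whether the choice matters.
- **Timing.** Report by arm the interval from referral, and from first clinical meeting, to the interview. Section 3.1 says that clinical meeting dates are recorded; the article does not say so for interview dates, so confirm that they are in the dataset.
- **Analyses by interval.** Label these descriptive. The timing arises after allocation and, given the immediate-help principle, may differ by arm. A subset chosen on it is not protected by randomisation.

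No new clinical measures are needed. The cost is SAP wording, modest extra analysis, somewhat less precise indirect effects and more modelling assumptions.
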